### Rejection criteria

Participants who breach the predetermined trial protocol at any point during the study period will be disqualified.

If a participant’s health condition destabilizes or demonstrates signs of deterioration throughout the course of the study, they will be promptly excluded.

Data sets that deviate from actual findings due to experimental equipment malfunctions or abnormalities will be rejected.

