### Interruption criteria

In the event of serious adverse events, if deemed significant by the attending physician, clinical observation for the individual case shall be immediately ceased.

Should the disease condition deteriorate during the clinical trial, or if other disease manifestations emerge that hinder the observation of the case, as assessed by the attending physician, the clinical trial will be halted.

Substantial deviations from the clinical trial protocol, including poor compliance or participants expressing reluctance to continue clinical observation and requesting withdrawal from the study to the supervising physician or investigator, will result in the termination of the subject’s involvement.

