### Statistical analysis

Statistical analyses were conducted utilizing IBM SPSS 26.0 software. In terms of descriptive statistics, qualitative indicators were represented by percentages, while quantitative indicators were summarized using means and standard deviations. For quantitative data, an independent samples t-test was applied when the data followed a normal distribution. In cases where normality assumptions were not met, the non-parametric Wilcoxon rank sum test was employed. Qualitative data were analyzed using the chi-square test, and rank data were examined with the Wilcoxon rank sum test. For datasets containing multiple observation time points, a repeated measures ANOVA was utilized to account for the longitudinal nature of the data. Statistical significance was determined at a P-value less than 0.05. For longitudinal data violating normality/sphericity, the non-parametric Friedman test replaced repeated measures ANOVA.

Given the limited sample size (N = 84) in this study, Multiple Imputation (MI) was employed to address missing data. This method generates multiple complete datasets and pools analysis results, thereby mitigating the bias associated with single imputation in small-sample studies. All imputation procedures were conducted using the MICE package in R, with five parallel imputations performed to ensure stability.

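### Randomised patients who breach the protocol, comply poorly or deteriorate are removed, and nothing keeps them in follow-up or analysis, so the randomised comparison could be biased

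*Protocol article*

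**What the plan says.** Two sections of the protocol article's Methods remove patients for events that can follow randomisation.

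- Rejection criteria, protocol breach: "Participants who breach the predetermined trial protocol at any point during the study period will be disqualified".
- Rejection criteria, worsening health: if a participant destabilises or "demonstrates signs of deterioration throughout the course of the study, they will be promptly excluded".
- Interruption criteria, serious adverse event, where the attending physician deems it significant: "clinical observation for the individual case shall be immediately ceased".
- Interruption criteria, compliance: "Substantial deviations from the clinical trial protocol, including poor compliance", "will result in the termination of the subject"'s involvement in the trial.
- Interruption criteria, worsening disease: "as assessed by the attending physician, the clinical trial will be halted".

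Under Statistical analysis, "Multiple Imputation (MI) was employed to address missing data", using MICE with five imputations. That section does not say whether disqualified, excluded or terminated patients are among those imputed.

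The Intervention section gives the experimental arm an additional 30 minutes a day, half of it supervised by a caregiver. Randomization and blinding states that patients and treating therapists cannot be blinded; the attending physician is not among the roles listed there as blinded. FMA-UE, the primary outcome, is due at baseline, at 4 weeks and at the 8-week follow-up.

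**The concern.** Randomisation makes the two sets of 42 comparable at entry. Removing patients afterwards, for reasons tied to how they are doing, can undo that. Deterioration and serious adverse events plausibly go with a lower FMA-UE. Poor compliance can depend on the arm, since one arm has an extra daily task to fail at. Breach and signs of deterioration carry no threshold, and some of the calls fall to people who may know the allocation.

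If one arm sheds more of its poor performers than the other, the remaining groups differ even when the treatment does nothing. At stake are the size of the FMA-UE difference and the false-positive rate of its test. An outcome that is never collected cannot be recovered later, and the article reports that recruitment is in progress.

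**Working it through.** **Side by side.** The rules act on the patient's place in the trial (disqualified, excluded, involvement ended, observation ceased), not only on study treatment. No section says that such patients are still assessed at 4 weeks and at follow-up, or are analysed as allocated. That leaves two readings of the imputation:

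1. Removed patients are dropped from the data set. Imputation then never reaches them.
2. Removed patients are kept and imputed. Under the usual missing-at-random assumption, a patient removed for deterioration is filled in from similar patients who did not deteriorate, so the imputed value tends to be too favourable.

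Neither reading restores the comparison by itself.

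**Scale from the plan.** The Sample size section gives 60.50 ± 2.19 and 59.14 ± 1.77. The pooled SD is √((2.19² + 1.77²)/2) = 1.991 and the difference is 1.36, so d = 1.36/1.991 = 0.683, as the plan states.

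**Illustration.** The article gives no removal rates, so these inputs are assumptions: 42 per arm; no true effect; a fraction q = 0.20 in each arm has a poor course; their outcome is lower by k = 1 or 1.5 SD, where SD means the spread within each class; a fraction r of the poor-course patients is removed and the rest are analysed by t-test.

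The share of poor-course patients left in an arm is f(r) = q(1 − r)/(1 − qr).

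- f(0.25) = 0.15/0.95 = 0.1579
- f(0.50) = 0.10/0.90 = 0.1111
- f(1) = 0

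The bias (experimental minus control) is k × [f(r control) − f(r experimental)]. Two-sided error rates come from simulation (6,000 to 20,000 trials per scenario).

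| Poor-course patients removed, experimental v control | Bias, k = 1 | Bias, k = 1.5 | Error |
|---|---|---|---|
| 25% v 25% | 0 | 0 | about 5% |
| 50% v 25% | 0.047 | 0.070 | about 5.4% to 6.5% |
| 100% v 25% | 0.158 | 0.237 | about 10% (k = 1), 14% to 15% (k = 1.5) |
| 25% v 100% | −0.158 | −0.237 | as the row above, against the intervention |

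**Units.** The mixture's total SD is √(1 + k² × 0.2 × 0.8): 1.077 for k = 1 and 1.166 for k = 1.5. In total-SD units the third row is 0.158/1.077 = 0.147 and 0.237/1.166 = 0.203. If the plan's 1.991 is taken as the total SD, that is 0.147 × 1.991 = 0.29 and 0.203 × 1.991 = 0.40 FMA-UE points, against a planned difference of 1.36.

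**A second model** removes the lowest patients on a latent score correlated 0.3, 0.5 or 0.8 with the outcome. With 20% of the experimental arm and 5% of control removed, the bias is 0.07, 0.11 and 0.18 SD, and the error 6.0%, 8.4% and 15.4%. With 20% removed from each arm, the mean bias is about 0.

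**The case against.** The strongest reply is that this is an article, an SAP may exist, and analysis sets are commonly defined there. That stands as far as it goes: the absence of a named intention-to-treat set is not the point made here, and planning imputation suggests that some patients with missing outcomes are meant to stay in. But an SAP cannot recover assessments that the protocol's rules prevented.

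It is also fair that the deterioration and adverse-event rules are worded alike for both arms. Only compliance has an evident source of asymmetry, and with equal removal the bias is about zero.

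Four stronger readings are tempting and are not supported:

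- **That the analysis will compare only compliant, stable patients.** The article names no analysis set and does not say that collected data are deleted. It could; that is all the text allows.
- **That every rule ends assessment at once.** Only the serious-adverse-event clause expressly ceases observation, and only if the physician deems the event significant. Disqualification, exclusion and ended involvement point the same way without saying so.
- **That rejecting data after equipment faults invites outcome-dependent removal.** The trigger is the fault, not the value. Among the listed outcomes only fNIRS is clearly equipment-based, so FMA-UE is hardly touched.
- **That a safety outcome is lost.** None is listed, and the triggering event is known by definition; only its later course could go unrecorded.

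Withdrawal at the patient's own request is a separate matter and is not criticised.

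**Conclusion.** The concern holds as a risk that the protocol creates by its own wording. It removes randomised patients for reasons that can relate to outcome and, for compliance, to arm; nothing keeps them in follow-up or analysis; and the planned imputation does not clearly cover them and would not fully correct for deterioration if it did.

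The size is not known from the documents. Under the assumptions above it runs from about zero with equal removal, through 0.05 to 0.07 SD with moderately unequal removal, to 0.16 to 0.24 within-class SD (about 0.15 to 0.20 in total-SD units) with strongly unequal removal. A reader might infer that the bias must favour Tai Chi. It need not: it would reverse if control lost more of its poor performers. The case for changing the text rests on the rules themselves, not on any one scenario.

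**What to change.** - Separate stopping study treatment from stopping outcome assessment. The first stays the physician's decision, and no clinical stopping rule is proposed here.
- Keep collecting FMA-UE at 4 weeks and at follow-up for every randomised patient unless consent for data collection is withdrawn.
- State that every randomised patient is analysed in the assigned arm, and that breach, poor compliance or deterioration is not a reason to drop a patient or data already collected.
- State that the imputation covers all randomised patients with missing outcomes, and add a sensitivity analysis for data not missing at random.
- Keep a per-protocol analysis as supportive.
- Reconcile the two deterioration clauses: the Interruption criteria speak of halting the clinical trial, the Rejection criteria of excluding the individual.

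The cost is protocol wording, a few outcome visits after treatment has stopped, and an estimated effect that may be slightly smaller than in compliers. Partly offsetting this, retaining all 42 per arm gives 87.1% power at d = 0.683 (two-sided t-test), against 79.2% with 34 per arm, which is roughly what the plan's 20% dropout leaves (42 × 0.8 = 33.6).

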### Interruption criteria

In the event of serious adverse events, if deemed significant by the attending physician, clinical observation for the individual case shall be immediately ceased.

Should the disease condition deteriorate during the clinical trial, or if other disease manifestations emerge that hinder the observation of the case, as assessed by the attending physician, the clinical trial will be halted.

Substantial deviations from the clinical trial protocol, including poor compliance or participants expressing reluctance to continue clinical observation and requesting withdrawal from the study to the supervising physician or investigator, will result in the termination of the subject’s involvement.

### Sample size

This trial aims to assess the impact of Tai Chi on upper limb function in post-stroke patients. Using G-power V.3.1.9.2 software for sample size calculation, the Fugl-Meyer Assessment Upper Extremity (FMA-UE) scale was selected as the primary outcome measure. Based on data from a previously published study [18], the mean FMA-UE scores post-intervention were 60.50 ± 2.19 for the Tai Chi group and 59.14 ± 1.77 for the control group. To detect the targeted effect size of 0.6830377 with a type 1 error rate of 5% (α = 0.05) and 80% statistical power (β = 0.20), a sample size of 64 participants is deemed sufficient. Accounting for a potential dropout rate of 20%, a total of 84 participants will be enrolled, with 42 participants assigned to each group.

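### The stated effect size needs 70 evaluable patients for 80% power, not 64, and 84 is neither figure correctly inflated for 20% dropout

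*Protocol article*

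**What the plan says.** The Sample size section of the protocol article bases the calculation on post-intervention FMA-UE results from an earlier published study: "60.50 ± 2.19 for the Tai Chi group and 59.14 ± 1.77 for the control group". From these it takes a "targeted effect size of 0.6830377", sets 5% type I error and 80% power, and states that "a sample size of 64 participants is deemed sufficient". The next sentence reads: "Accounting for a potential dropout rate of 20%, a total of 84 participants will be enrolled", which is 42 per group.

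The section names G*Power but neither a test nor its sidedness. Under Statistical analysis, for quantitative data, "an independent samples t-test was applied when the data followed a normal distribution", with a rank sum test as fallback and repeated measures ANOVA for several time points. The significance rule there is "Statistical significance was determined at a P-value less than 0.05", again without sidedness. Allocation is 1:1 (Randomization and blinding).

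**The concern.** The section gives every numerical input to a standard two-group calculation, so 64 and 84 should both follow from it. A standardised effect of 0.68 usually calls for rather more than 32 per arm at two-sided 5% and 80% power. Separately, 64 divided by 0.8 is plainly not 84.

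This paragraph is the trial's whole justification for its size. If its two main numbers disagree, a reader cannot tell which evaluable number the trial relies on, or whether the planned enrolment protects the stated power against the planned loss. Loss is a real prospect here: the Rejection and Interruption criteria remove participants for protocol breaches, deterioration and poor compliance.

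**Working it through.** **Inputs** (Sample size section unless noted)
- Means and SDs: 60.50 (2.19) and 59.14 (1.77)
- Type I error 0.05, power 0.80, dropout 20%
- Allocation 1:1 (Randomization and blinding)
- Independent samples t-test (Statistical analysis)
- Sidedness is not stated; two-sided is assumed and one-sided is also tried.

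**1. Effect size**

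Pooled SD = √[(2.19² + 1.77²)/2] = √[(4.7961 + 3.1329)/2] = √3.9645 = 1.9911.

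d = (60.50 − 59.14)/1.9911 = 1.36/1.9911 = 0.68304.

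This agrees with the protocol's figure, so the calculation described is a comparison of two post-intervention means.

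**2. Evaluable number**

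Exact power of the two-sample t-test comes from the noncentral t distribution with n₁ + n₂ − 2 degrees of freedom and noncentrality d·√[n₁n₂/(n₁ + n₂)]. For 32 per arm this is 0.68304 × √16 = 2.732 on 62 df, against a two-sided critical value of 1.999.

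| Per arm | Total | Two-sided power | One-sided power |
|---|---|---|---|
| 27 | 54 | – | 79.7% |
| 28 | 56 | – | 81.0% |
| 32 | 64 | 76.7% | 85.5% |
| 33 / 34 | 67 | 78.6% | – |
| 34 | 68 | 79.2% | 87.3% |
| 35 | 70 | 80.4% | 88.2% |
| 42 | 84 | 87.1% | 92.8% |

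The smallest total reaching 80% is 70 two-sided and 56 one-sided. The normal approximation gives 68 and 54. None of these is 64.

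**3. Dropout step**

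The number to enrol is the evaluable number divided by (1 − dropout).

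- From 64: 64/0.8 = 80. The common mistake of multiplying gives 64 × 1.2 = 76.8. Neither is 84.
- Going from 64 to 84 implies a loss of 20/84 = 23.8%, not 20%.
- From 70: 70/0.8 = 87.5, so 88. The multiplying mistake gives 70 × 1.2 = 84 exactly.

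That last match suggests 70 was the calculated number, was multiplied by 1.2, and 64 is a slip. This is only an inference, since 70 appears nowhere in the document.

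**4. What 84 delivers**

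- No loss: 87.1% two-sided power.
- 20% loss: 84 × 0.8 = 67.2, so about 67 evaluable and 78.6%.
- Loss at which 70 remain: 1 − 70/84 = 16.7%.

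**The case against.** The strongest objection is that the section states neither sidedness nor test. One-sided, 64 gives 85.5% power, and the protocol calls 64 sufficient rather than minimal, so on that reading the sentence is literally true. Other routes also lead to 64: a one-sided t-test at 85% power, a one-sided rank sum test under the minimum asymptotic relative efficiency of 0.864, or the between-group F-test of a repeated measures ANOVA with f = d/2 = 0.3415. The last gives 64 with two measurements correlated at 0.80, or three at 0.85, and the protocol does name repeated measures ANOVA.

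This shows that 64 is not impossible under every analysis. It does not show that 64 follows from what is written. The one-sided t-test at the stated 80% power returns 56. The other routes need a power, an efficiency bound or a correlation that the document does not state; for the F-test, assumed correlations from 0.5 to 0.95 give anything from 48 to 68. The section reports a Cohen's d on post-intervention means, which points to the t-test. No route repairs the step from 64 to 84.

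Two points on size stand. The shortfall is small: 78.6% against 80%, or three evaluable patients. If 64 is taken at face value, 84 exceeds the 80 needed. It is also true that multiple imputation is planned, so a complete-case count of 67 is not exactly the planned analysis, but imputation does not restore lost information.

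**Conclusion.** The concern holds. The effect size is right, but the evaluable number does not follow from the stated inputs, and the enrolled number does not follow from the evaluable number.

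The mismatch between 64 and 84 is plain arithmetic and depends on no assumption. That 64 falls short (76.7% power, 70 needed) rests on a two-sided, two-sample t-test at a single time point, which is the conventional reading of the section. Under that reading, planned enrolment with planned loss misses the stated power by 1.4 percentage points. The consequence for the trial is therefore modest, but the paragraph is wrong as written and should be corrected.

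**What to change.** Rewrite the Sample size section to:

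- name the two-sided two-sample t-test at 5%;
- replace 64 with 70 evaluable participants (35 per arm) for 80% power at d = 0.683;
- keep 84 enrolled (42 per arm), and state that this gives about 79% power at 20% dropout and at least 80% at up to 16.7% dropout.

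If the sponsor prefers to hold 80% power at the full 20% loss, enrolment would be 88 (44 per arm), four more than planned. If 64 came from a different calculation, the section should name its test, sidedness and any correlation used, and the dropout step must still be redone.

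With 84 kept, the cost is a text correction and a slightly less favourable power statement, with no extra patients. The Trial status section reports that recruitment is still in progress, so the correction can be made before analysis.

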### Randomization and blinding

Eligible subjects who fulfill the inclusion criteria and provide signed informed consent will undergo randomization, allocated in a 1:1 ratio to either the control or intervention groups. The randomization process will be computer-generated using a block randomization design with a fixed block size of 4, implemented by independent statistical experts blinded to study details. The random allocation sequence will be produced using SPSS software to ensure randomness and reproducibility. To maintain the integrity of the randomization, therapists not directly involved in recruitment, assessment, or intervention will securely place each allocated number into an opaque envelope. Following patient screening, the recruitment physician will liaise with a designated coordinator who will then dispatch the necessary documentation to eligible subjects, informing them of their group assignment. This rigorous randomization procedure aims to minimize bias and ensure the validity of the study results.

Owing to the inherent characteristics of the intervention, it is not feasible to blind the subjects and therapists directly involved in the intervention process. However, throughout the duration of the study, the therapist conducting assessments, the researcher tasked with data collection, and the statistician analyzing the data will remain blinded to group allocations. This blinding protocol will be maintained until the completion of statistical analyses to minimize potential bias. Once the statistical analyses are concluded, the blinding will be lifted.

### Intervention

Both groups received conventional rehabilitation therapy, with the rehabilitation plan based on assessment. The regular treatment included muscle strength training, sensory training, functional activity training, seated balance training, acupuncture, biofeedback therapy, and more. The total duration of the therapy was 3 hours per day, 5 days a week, for a total of 4 weeks. The experimental group received an additional 30 minutes of seated Tai Chi Yunshou training, consisting of a 15-minute one-by-one session with an experienced Tai Chi therapist in the morning, followed by a 15-minute seated Tai Chi Yunshou practice in the afternoon under the supervision of a caregiver.

### Control group

The control group solely adhered to a program of conventional comprehensive rehabilitation training which consists of physical therapy, acupuncture, Tuina, speech therapy if necessary. Physical therapy includes rolling, side lying to sitting, sitting training, sitting to standing, walking training. motor control training, muscle strength training, Tuina massage for 60 mins.

The acupuncture protocol involved a standardized selection of points categorized by anatomical region: Scalp and Face: Baihui (GV20), Sishencong (EX-HN1), Tianzhu (BL10), and Lianquan (RN23). Upper Limb: Jianyu (LI15), Quchi (LI11), Waiguan (TE5), and Hegu (LI4). Lower Limb: Huantiao (GB30), Zusanli (ST36), Xuanzhong (GB39), Sanyinjiao (SP6), and Taichong (LR3) [19]. All acupoints were stimulated using a manual high-frequency, small-amplitude twirling technique, administered by licensed practitioners with ≥5 years of clinical experience. Needle retention lasted 20 minutes per session.

To safeguard the well-being of the participants, a one-on-one training modality was implemented between the therapist and subjects. This arrangement ensured that training was discontinued promptly in the event of subject-reported fatigue or any discomfort.

### Experimental group

The intervention program for the test group entailed a combination of seated Tai Chi Yunshou exercises and routine comprehensive rehabilitation training [11]. Under the guidance of the therapist, patients were taught the seated Tai Chi Yunshou exercises.

Specific training methods are as follows: 1. starting position. Sit on a stable chair or bed with both feet flat on the ground, shoulder-width or slightly wider. Let both hands hang naturally at your sides, relax whole body, and look straight ahead. Keep spine naturally straight, without leaning too much forward or backward. 2.Beginning the Movement (Left Yunshou as an Example). Slowly lift left hand from the left side of body, palm facing inward, while simultaneously lifting right hand to chest, palm facing downward. Turn upper body slightly to the left, and as turning, move left hand in an upward arc to the left, gradually flipping palm outward. At the same time, move right hand in a downward arc to the right, palm facing downward. Continue moving left hand in an arc to the left and backward, palm facing outward, while simultaneously moving right hand in an arc from the front of abdomen to the left and upward to left chest, palm facing inward. Follow the movement of left hand with eyes, keeping head straight and avoiding tilting or tilting up and down.3. Alternate Movement. Next, perform the Right Yunshou, with movements opposite to the Left Yunshou. Alternate between the two hands to create a continuous flow of Yunshou movements. Pay attention to maintaining body stability, using the waist as the axis to drive the hands in arcs.

